## Abstract

**Background:**

Metabolic syndrome (MetS) significantly increases the risk of major adverse cardiovascular events (MACE), yet evidence-based complementary therapies remain limited. Tongmai Jiangtang Capsule (TJC), a traditional Chinese medicine (TCM) compound, has demonstrated benefits for glycolipid metabolism and microvascular complications, but its effect on hard cardiovascular and cerebrovascular (CCV) endpoints remains unconfirmed.

**Objective:**

To explore whether TJC, as an adjunctive therapy to standard care, reduces the incidence of MACE in patients with MetS and Qi deficiency-blood stasis syndrome.

**Methods:**

This is a randomized, double-blind, placebo-controlled, multicenter trial. A total of 530 participants aged ≥65 years, diagnosed with MetS and the TCM pattern of Qi Deficiency and Blood Stasis, and at high CCV risk, will be enrolled. They will be randomly assigned (1:1) to receive either TJC or a matched placebo, in addition to standard care, for 26 weeks, followed by a 26-week follow-up. The primary endpoint is the composite of 3P-MACE (cardiovascular death, non-fatal myocardial infarction, non-fatal stroke). Secondary endpoints include metabolic parameters, vascular assessments, TCM symptom scores, and quality of life. Omics analyses will explore potential mechanisms. The trial was registered on ClinicalTrials.gov (NCT06908473).

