### Study procedure

The schedule of study procedures is outlined in Table 1. The study will include a screening/baseline period, a treatment period, and a follow-up period. The screening/baseline period will last 2 weeks, the treatment period will be 26 weeks, and the follow-up period will be 26 weeks. Patients will be required to provide written informed consent after a complete explanation of the study during the screening period.

**Table 1 T1:** Study schedule.

Research phase	Screening/baseline	Treatment phase			Observation phase after intervention
Number of visits	Visit 1	Visit 2	Visit 3	Visit 4	Visit 5
Visit time point	D-7–0	Week 4 ± 4 days	Week 12 ± 4 days	Week 26 ± 4 days	Week 52 ± 4 days

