**Data collection**					
Written informed consent	□				
Inclusion/exclusion criteria	□				
Demographics	□				
Obtain central random number	□				
Previous history, medical history, and allergies	□				
Comorbidities and co-medications	□	□	□	□	□
Safety evaluation					
Vital signs and physical examination	□	□	□	□	□
Blood routine, Urine routine, Fecal routine	□		□	□	
Liver function(ALT, AST, ALB), kidney function(UN, Cr, UA, eGFR)	□		□	□	
12-Lead ECG	□		□	□	□
Efficiency evaluation					
Composite outcome measures	□	□	□	□	□
Preset exploration indicators	□	□	□	□	□
BMI, waist to hip ratio, body fat analysis	□	□	□	□	□
Blood glucose, blood lipids, blood pressure	□		□	□	□
Fasting insulin, C-peptide, HOMA-IR	□		□	□	□
Cardiovascular and cerebrovascular risk index	□		□	□	□
Troponin, cardiac enzymes, BNP	□		□	□	□
Vitamin D	□			□	□
UACR	□		□	□	□
Cardiac color doppler ultrasound	□			□	□
Neck vascular ultrasound	□			□	□
Traditional chinese medicine syndrome points	□	□	□	□	□
Quality of life rating	□	□	□	□	□
Omics analysis	□			□	

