### Outcome measures

#### Primary outcome

Composite Endpoint (35)
Death due to cardiovascular and cerebrovascular reasons:
1.1.Death due to cardiac arrest (with symptomatic myocardial ischemia, new ST-segment elevation or left bundle branch block, and angiographic or autopsy evidence of new thrombosis).1.2.Death due to cardiovascular causes: caused by acute myocardial Infarction (MI), heart failure, stroke, other cardiovascular causes, or without clear non-vascular cause.1.3.Sudden cardiac death: unexpected death due to cardiac causes in a previously stable condition.1.4.Death occurring within up to 30 days after a documented acute MI, without conclusive evidence of another cause; or death occurring based on clinical presentation and ECG evidence before biomarker confirmation of myocardial necrosis.1.5.Death occurring within up to 30 days after an intracranial hemorrhagic or non-hemorrhagic stroke, based on clinical presentation, neuroimaging, or autopsy, without conclusive evidence of another cause of death.1.6.Other cardiovascular or cerebrovascular causes of death.Non-fatal myocardial infarction (MI):
2.1.Spontaneous MI.2.2.ST-segment elevation MI (STEMI).2.3.Non-ST-segment elevation MI (NSTEMI).2.4.Percutaneous coronary intervention (PCI)-related MI.2.5.Coronary artery bypass grafting (CABG)-related MI.2.6.Silent acute MI.Non-fatal stroke:
3.1.Acute neurological dysfunction attributed to a vascular cause, documented by CT or MRI, with other causes excluded.3.2.Transient ischemic attack with symptoms lasting <24 h but with corresponding new imaging evidence (optional predefined criterion, might be moved to secondary depending on standard definitions).3.3.Micro-bleeds: small, round, hypointense lesions <5-10 mm on MRI (often considered a biomarker rather than a clinical event; might be more suitable for exploratory/system bio indicators).

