### Sample size calculation

This is a two-arm, randomized, controlled superiority trial with a placebo control group and a TJC group. Using the composite primary outcome measure and a superiority test for proportions for sample size estimation. Based on literature, the estimated difference between the two groups is 15% (27, 38). With a one-sided *α*=0.025 and power (1-*β*) of 90%, using PASS 15 software for a 1:1 allocation ratio, and accounting for a potential 20% dropout rate (due to loss to follow-up, refusal, exclusion, etc.), a minimum of 265 subjects per group is required, resulting in a total sample size of at least 530 subjects.

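### The primary 3P-MACE proportion, and the 15% difference and 90% power built on it, are tied to no time window, though the design offers two (week 26 and week 52)

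*Protocol article*

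**What the plan says.** The Abstract has patients treated "for 26 weeks, followed by a 26-week follow-up. The primary endpoint is the composite of 3P-MACE", with no time point attached to the composite. It defines the endpoint by its components: "The primary endpoint is the composite of 3P-MACE (cardiovascular death, non-fatal myocardial infarction, non-fatal stroke". The Primary outcome section does the same at greater length, starting from "Death due to cardiovascular and cerebrovascular reasons", and gives no week.

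The Study procedure section sets out the two periods: "the treatment period will be 26 weeks, and the follow-up period will be 26 weeks". Table 1 heads the second period "Observation phase after intervention". Its row "Composite outcome measures" is ticked at baseline and at weeks 4, 12, 26 and 52, and no visit is marked as primary.

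The Sample size calculation works on event proportions: "Using the composite primary outcome measure and a superiority test for proportions for sample size estimation". The effect is given as "Based on literature, the estimated difference between the two groups is 15% (27, 38"), with one-sided alpha 0.025, 90% power, 1:1 allocation, 20% dropout and 265 per group. It states neither the rate expected on placebo nor the time by which events are counted.

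The Statistical analysis section lists chi-square or Fisher tests for categorical data, the Cochran-Mantel-Haenszel method for centre, analysis of all randomised patients by intention to treat, and LOCF for missing data in the primary analysis. It names no time point and no time-to-event method.

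**The concern.** A cumulative proportion changes with the window over which it is counted. By week 26 it describes events while study drug is being supplied. By week 52 it describes events over a year in which drug was supplied for the first half only. A reader cannot tell which of these the trial sets out to show.

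The time point is part of the primary endpoint. The article gives the endpoint definition, the scale of comparison, the effect size and the power, so the missing window is not a technical detail of the kind usually left to an analysis plan. Without it, the 15% and the 90% belong to no defined quantity and cannot be checked for plausibility.

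**Working it through.** **Inputs from the protocol article.** Difference 0.15 in proportions; one-sided alpha 0.025 (z = 1.960); power 0.90 (z = 1.282); 1:1 allocation; 20% dropout; 265 per arm, hence 265 × 0.80 = 212 evaluable per arm; 26 weeks on drug followed by 26 weeks off.

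**Assumptions, because the article gives no rates.** A pair of proportions that returns 265 per arm, and a constant hazard within each period.

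**Step 1: the plan's own figure.** With p̄ the mean of the two proportions,

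n = [1.960·√(2p̄(1−p̄)) + 1.282·√(p₁(1−p₁) + p₂(1−p₂))]² / (p₁−p₂)², then divided by 0.80.

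At a 15-point difference, the size per arm after dropout runs from 79 (15% against 0%) to 290 (57.5% against 42.5%). It equals 265 at about 43% against 28%, or at the mirror pair of about 72% against 57%. For 43% against 28%: [1.960 × 0.6767 + 1.282 × 0.6684]² / 0.0225 = 211.8, so 212, and 212/0.80 = 265. The figure of 265 is therefore attainable, but it identifies no window.

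**Step 2: moving between windows.** Under a constant hazard, a 52-week risk p becomes 1 − √(1−p) at 26 weeks, and a 26-week risk p becomes 1 − (1−p)² at 52 weeks. Power with 212 per arm is

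Φ{[|p₁−p₂|·√212 − 1.960·√(2p̄(1−p̄))] / √(p₁(1−p₁) + p₂(1−p₂))}.

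**Step 3: if the 15 points refer to week 52 (43% against 28%).** The hazard ratio is ln(0.72)/ln(0.57) = 0.584.

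| Window and effect | Placebo | TJC | Difference | Power | Needed per arm, with dropout |
|---|---|---|---|---|---|
| Week 52, constant hazard ratio | 43.0% | 28.0% | 15.0 | 90.0% | 265 |
| Week 26, same hazard ratio | 24.5% | 15.1% | 9.4 | 67.7% | 475 |
| Week 52, same hazard ratio on drug only | 43.0% | 35.9% | 7.1 | 31.8% | 1,257 |

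In the last row the TJC risk is 1 − √0.72 × √0.57 = 0.359.

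**Step 4: if the 15 points refer to week 26 (43% against 28% by then).**

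| Window and effect | Placebo | TJC | Difference | Power | Needed per arm, with dropout |
|---|---|---|---|---|---|
| Week 26 | 43.0% | 28.0% | 15.0 | 90.0% | 265 |
| Week 52, no effect after stopping | 67.5% | 59.0% | 8.6 | 44.6% | 834 |
| Week 52, same hazard ratio persisting | 67.5% | 48.2% | 19.3 | 98.3% | 169 |

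**Reading.** With the same 530 patients, power at the window or effect pattern not used for planning runs from about 32% to about 98%. Its direction depends on whether the effect outlasts treatment.

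**The case against.** Five points can be made for the plan.

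1. **The analysis plan comes before unblinding.** The Statistical analysis section says a detailed SAP is to be settled before database lock and unblinding, and the Blindness section keeps investigators, subjects and site staff blinded until lock. A reader might infer that two possible windows inflate the false-positive rate. If the better of the two tests were picked, two-sided error would be about 8.3% (7.8% to 8.8% for correlations of 0.8 to 0.6; 0.707 corresponds to equal event rates in both halves). That requires choosing the window after seeing unblinded results, which the stated sequence should prevent. The inflation is not a property of the plan as written.

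2. **Week 52 is the more natural reading.** Events are collected to week 52, the analysis is by intention to treat, and the Introduction says such events need long observation. Nothing suggests that events after week 26 would be discarded. This makes week 52 likelier, but it does not designate it: week 26 carries the same tick and is the end of treatment.

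3. **Low power in either window is a different matter.** A reader might go further and conclude that the trial has very little power whichever window is used. Assuming a ratio of 0.70 on drug and placebo rates of 10% to 20% per year gives only 12% to 19% at week 26. None of those inputs is in the article, and the figures mainly reflect an effect smaller than 15 points. Even the ordering is not fixed: at week 52 the same inputs give 7% to 11% if the effect stops with the drug and about 18% to 33% if it persists.

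4. **The primary test is partly inferred.** Proportions are stated for sizing. The analysis section offers a menu by data type and does not name the test for 3P-MACE. Chi-square or Fisher is the likely reading, and the only one the text offers for a binary outcome.

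5. **A missing week needs only a week.** Naming the window and its rates would close the gap itself. The time-to-event analysis is an added improvement, justified under the fix.

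**Conclusion.** The point stands in this form: the primary proportion has no window, and the 15% difference and 90% power therefore attach to no defined estimand and cannot hold for both windows. On the assumed pair of 43% against 28% at week 52, power is 90% at week 52, about 68% at week 26, and about 32% at week 52 if the effect is confined to the treatment period. These figures rest on assumed rates, constant hazards within each period and 212 evaluable per arm. They show how much the choice matters and do not predict the trial's power. The documents support neither an inflated type I error under the planned sequence nor a claim that one window is always the stronger.

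**What to change.** Before unblinding, name one primary window in the protocol and carry it into the SAP. We suggest time from randomisation to first 3P-MACE adjudicated by the Clinical Events Committee, through week 52, in all randomised patients whether or not they remain on drug. Compare arms by a centre-stratified log-rank test, report a Cox hazard ratio, and censor dropouts at last contact.

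This would replace a chi-square or Fisher test on LOCF-completed proportions. Under LOCF, a patient who leaves without an event is carried forward as event-free to the end. With 20% dropout planned for, that matters, whereas censoring uses only the time actually observed.

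Label the same analysis cut at week 26 as supportive, for the treatment period. Then state the expected event rate in each arm for the named window, with its source, and restate the difference and power from those rates.

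**Cost.** Protocol and SAP wording, plus one recalculation. Table 1 already collects the composite to week 52, so no visit or data item is added. The restated power may look less favourable. If the effect fades after treatment stops, the hazard ratio through week 52 will be an average over two unlike periods, which is why the week-26 analysis should be reported beside it.

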**Discussion:**

This rigorously designed trial is expected to provide high-level evidence regarding the role of TJC in preventing CCV events in MetS. If positive, it will offer a novel, multi-target integrative treatment strategy. The findings will also advance the evidence-based evaluation of TCM compounds and contribute to chronic disease prevention goals. Regardless of the primary outcome, the mechanistic insights will inform future research on formula optimization and precision intervention.

**Clinical Trial Registration:**

https://clinicaltrials.gov/expert-search?term=NCT06908473, identifier, NCT06908473.

## Introduction

Metabolic Syndrome (MetS) represents a significant global public health challenge in the 21st century (1). It is characterized by a cluster of core components including central obesity, hyperglycemia, hypertension, and dyslipidemia (elevated triglycerides/reduced high-density lipoprotein cholesterol) (2). Its pathophysiological essence involves the superimposition of insulin resistance (IR)-mediated metabolic disorders and a state of chronic low-grade inflammation (3–5). Since its first formal definition by the World Health Organization (WHO) in 1998 (6), the prevalence of MetS has experienced exponential growth, paralleling the global rise in obesity rates and population aging. The latest Chinese epidemiological data (2023 Report on Chronic Diseases and Risk Factors Surveillance in China) indicates that the prevalence of MetS among adults has reached 31.2%, with a notable trend towards younger age groups—the prevalence among individuals under 40 has increased by 47% compared to a decade ago. This population faces not only a high risk of metabolic diseases such as diabetes and non-alcoholic fatty liver disease but also (7–9), due to vascular endothelial injury and accelerated atherosclerosis induced by metabolic disturbances, constitutes a “high-risk group” for cardiovascular and cerebrovascular events (5, 10–12) (e.g., myocardial infarction, stroke). Studies have shown that the risk of cardiovascular events in patients with MetS is 2.3-3.1 times that of healthy individuals, with all-cause mortality increased by 1.8-2.5 times; among these, MetS patients with comorbid diabetes have a 10-year risk of cardiovascular and cerebrovascular events exceeding 40% (13–15). However, current clinical management of MetS predominantly focuses on intervening in individual risk factors (e.g., glucose-lowering, blood pressure control, lipid regulation), lacking multi-target intervention strategies aimed at the “metabolic-vascular injury” network (16). Furthermore, some pharmacological agents (e.g., long-term use of statins, insulin) are associated with side effects such as hepatic and renal impairment and hypoglycemia, making it difficult to meet patients’ needs for “safe, efficient, and holistic regulation” therapeutic approaches. Recent large cardiovascular outcome trials (17, 18) have shown that in high-risk populations with obesity and cardiovascular disease, the annual MACE rate remains substantial despite contemporary standard care.

Traditional Chinese medicine (TCM) compounds, by virtue of their “multi-component, multi-target, multi-pathway” intervention characteristics, offer novel insights for the comprehensive management of MetS. Meta-analyses have shown that TCM or the combination of TCM and Western medicine can effectively improve metabolic syndrome and reduce cardiovascular and cerebrovascular risk (19–21). Tongmai Jiangtang Capsule (TJC) is an innovative proprietary Chinese medicine developed independently, derived from the classical empirical formula “Method for Boosting Qi, Activating Blood, and Dredging Collaterals.” Its main components include Astragalus membranaceus (Huangqi), Salvia miltiorrhiza (Danshen), Ligusticum chuanxiong (Chuanxiong), Hirudo (Shuizhi), and Pheretima (Dilong), among others. Modern pharmacological studies have confirmed that its core active ingredients (e.g., astragaloside IV, tanshinone IIA, ligustrazine) can ameliorate metabolic disorders through multiple mechanisms (22–26): On one hand, astragaloside IV can activate the AMPK pathway—a key energy sensor that not only enhances insulin sensitivity and inhibits hepatic gluconeogenesis but also exerts anti-inflammatory effects by suppressing NF-*κ*B signaling—thereby ameliorating metabolic disorders; tanshinone IIA can downregulate the expression of inflammatory cytokines (TNF-α, IL-6) in adipose tissue, alleviating IR. On the other hand, ligustrazine and hirudin can inhibit platelet overactivation, reduce hypercoagulability, and simultaneously improve vascular endothelial function and delay the formation of atherosclerotic plaques by modulating the endothelin-1 (ET-1)/nitric oxide (NO) balance. Preliminary studies have indicated that TJC has beneficial effects on both macro- and micro-vascular complications of diabetes, with a good safety profile (27–32); however, its impact on hard cardiovascular and cerebrovascular endpoints (e.g., myocardial infarction, stroke, cardiovascular death) remains unclear.

Currently, clinical research on interventions for cardiovascular and cerebrovascular risk in MetS predominantly focuses on Western drugs (e.g., GLP-1 receptor agonists, SGLT2 inhibitors) or single TCM components (e.g., Salvia miltiorrhiza injection). Large-scale, multi-center, long-term follow-up randomized controlled trials (RCTs) investigating TCM compounds, particularly Tongmai Jiangtang Capsule, are still lacking. The complexity and heterogeneity of MetS components, coupled with its insidious progression, necessitate multi-center collaboration to enroll populations from different regions and with diverse lifestyles, thereby enhancing the generalizability of the findings. Furthermore, the occurrence of cardiovascular and cerebrovascular events requires a long observation period. A double-blind design can mitigate observation bias and ensure the objectivity of efficacy assessment. Additionally, existing research on TCM compounds often focuses on short-term improvements in metabolic parameters, lacking comprehensive validation of the “metabolism-vascular-event” cascade, making it difficult to answer the core clinical question: “Can it ultimately reduce the risk of cardiovascular and cerebrovascular events?”

Therefore, conducting this study holds significant scientific and clinical value: Firstly, through a rigorously designed large-sample RCT, it aims to clarify the effect of TJC on cardiovascular and cerebrovascular events (including non-fatal myocardial infarction, non-fatal stroke, and cardiovascular death) in patients with MetS, filling the gap in high-level evidence for TCM compounds in this field. Secondly, it will systematically explore the potential mechanisms by which TJC improves cardiovascular and cerebrovascular risk, providing experimental support for its theory of “holistic regulation and multi-target intervention.” Thirdly, it will provide a new evidence-based approach for the integrated traditional Chinese and Western medicine treatment of MetS, promote the standardized application of TCM in chronic disease prevention and control, and contribute to achieving the comprehensive chronic disease prevention and control goals of “Healthy China 2030”.

In summary, this study addresses the global epidemic trend of MetS and unmet clinical needs, with the core objective of “verifying the impact of a glucose- and lipid-regulating TCM compound on hard cardiovascular and cerebrovascular endpoints.” Through rigorous design and scientific implementation, it is expected to provide new strategies for the prevention and treatment of MetS, offering significant social benefits and academic value.

## Methods/design

### Study objectives

The purpose of this study is to evaluate the effect of TJC on cardiovascular and cerebrovascular events in MetS patients with high cardiovascular risk. We hypothesize that TJC, as an add-on to standard Western medical treatment, can improve glycolipid metabolism and reduce cardiovascular and cerebrovascular events in patients with high cardiovascular and cerebrovascular risk and MetS (HCR-MetS). If the hypothesis holds, this study will provide clinical evidence for TJC in treating HCR-MetS.

### Study design

This is a multicenter, randomized, double-blind, placebo-controlled, parallel-group superiority trial. The study protocol adheres to the Standard Protocol Items: Recommendations for Interventional Trials (SPIRIT) 2013 guidelines (18) and the CONSORT Extension for Chinese Herbal Medicine Interventions (19). The study was prospectively registered on ClinicalTrials.gov in April 2025 (NCT Number: NCT06908473). The study flow chart is shown in Figure 1.

**Figure 1 F1:**
[figure not shown]
Schedule of the trial. HCR-MetS, high cardiovascular and cerebrovascular risk metabolic syndrome; TJC, Tongmai Jiangtang capsules; AES, adverse events.

### Setting and participants

The study will be conducted at six research sites in China (Guangdong Provincial Hospital of Traditional Chinese Medicine, Traditional Chinese Medicine hospital of Sichuan Province, Xiyuan Hospital of China Academy of Chinese Medical Sciences, Shanxi Provincial Hospital of Chinese Medicine, First Teaching Hospital of Tianjin University of Traditional Chinese Medicine, The First Affiliated Hospital of Guangzhou University of Chinese Medicine), located in southwest, northwest, central, north, and south China. Recruitment strategies will include advertisements on social media, as well as posters displayed at the six participating institutions. Recruitment will commence in May 2025 and is expected to be completed within 3 years. Patients who agree to participate will be examined and diagnosed by an associate chief physician to confirm their eligibility for the study.

